## Appy CDS Project Consort Diagram- Draft

[figure not shown]

## 7) Reporting and Data Storage

### a) Capturing Transfer Patients

One of the unique challenges of this project at the prime site is that many children in this age group are transferred to another hospital for additional follow up or surgery. A subset of patients presenting to a HealthPartners or HealthPartners affiliated ED who are eligible for Appy CDS will most likely be transferred to Children's Hospitals of Minnesota for definitive surgical care. In order to evaluate final diagnoses for these patients, a process for identifying and linking patients has been developed and is outlined in Figure 3.

**Figure 3. Process for Identifying and Linking Transferred Patients**

[figure not shown]

Data transfers will occur on a monthly basis. The limited data set sent from HP to Children's will include a study ID, date of birth, sex, arrival date, discharge date, reason for encounter, disposition, and discharge disposition of patients that were transferred from a HealthPartners facility to Children's. Files will be sent through secure file transfer and password protected. The above figure illustrates the process for capturing transfer patients and evaluating final outcomes.

In other cases, if patients are transferred out of the HP or KP system for surgery and we are unable to review the operative and pathology notes we will exclude them from the primary analyses because we cannot confirm appendicitis based on our definition. In sensitivity analyses we will explore inclusion of these patients with classification of final diagnosis (appendicitis versus other surgical or medical condition) based on diagnosis at the time of transfer.

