#### a) Exclusion Criteria

Using data from the EHR and gathered from triage-based prompts introduced at all participating EDs, we will identify patients with a current pregnancy, previous abdominal surgery, trauma, cystic fibrosis, sickle cell anemia, inflammatory bowel disease, or other selected comorbidities at the prime site, or with an ED visit for abdominal pain in the prior 7 days. These patients will be excluded from the study cohort. As described below, based on responses to the initial screening questions, patients with >120 hours of abdominal pain or patients with no right sided or generalized abdominal pain will also be excluded from the risk score calculation and further analyses.

If patients are transferred to an outside facility (outside of KPNC or HealthPartners networks) for surgery *and* we are unable to review their operative and pathology notes, they will be excluded from the safety analyses. These patients will be retained in the primary analyses, evaluating the use of CT or US, with the diagnosis of appendicitis or not appendicitis assigned based on provider impression and imaging available at the time of ED discharge / transfer.

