### Identification of a cohort of patients with acute abdominal pain at risk for appendicitis (Hypothesis 1):

Using existing EHR data and simple prompts implemented at triage at all 17 sites over the 6-month pre-intervention period and 24-month trial we will identify our study cohort of children and adolescents at elevated risk for appendicitis. The algorithm underlying this tool will exclude patients with chronic abdominal pain, abdominal trauma, and/or pregnancy, because their management is beyond the scope of the proposed intervention. For patients undergoing an appendectomy within 7 days of their index ED visit, a trained, blinded nurse abstractor will review their pathology report. For patients undergoing appendectomy, appendicitis is defined by specific terminology on the pathology report, as in our previous multicenter study (consistent with appendicitis, neutrophil invasion of tissue, serosal inflammation, acute peri-appendicitis, or acute appendicitis). For patients with perforation undergoing drainage and/or intravenous antibiotics and interval appendectomy, diagnosis will be based on clinical notes from the treating surgeon. For patients transferred from the ED where they initially sought care to a facility with pediatric surgical expertise, we will seek final diagnoses and pathology reports from the receiving institution. If we are unable to verify final diagnosis, the patient will be excluded from primary analyses. These patients may be included sensitivity analyses with the diagnosis of appendicitis or not appendicitis assigned based on provider impression and imaging available at the time of ED discharge / transfer. For HPMG, outside of the study EDs, Children's Hospital would be the primary outside institution to receive transfers for further evaluation and appendectomy. Thus, we will establish a registry of patients with a discharge diagnosis of appendicitis from Children's Hospital and use a probabilistic method to determine whether these patients are matches with patients receiving care in the HPMG study EDs. KPNC uses a hub and spoke system for pediatric surgery. Among the 11 CREST sites are four pediatric surgical hubs.

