**Appendiceal perforation, negative appendectomies, and missed appendicitis** (safety outcomes): Although it is unlikely that the Appy-CDS will significantly increase rates of adverse events, the following clinical or safety outcomes will be monitored both before and during the full Appy-CDS intervention. *Appendiceal perforation* will be evaluated in patients who undergo appendectomy based on chart review of the surgeon's intra-operative note. As in our previous work, perforation will be defined by keywords in the operative report (presence of abscess, peritonitis, complex appendicitis, or purulent material). In addition, we will review all charts for patients with a discharge diagnosis of perforated appendicitis (ICD-9 540.1) who do not undergo an appendectomy during their index hospitalization, because a subset of patients with appendiceal perforation (4% in our previous multicenter cohort, unpublished data) will be admitted for intravenous antibiotics and undergo an interval appendectomy 6-12 months later. *Negative appendectomies* are appendectomies in which the pathology report reveals no evidence of appendiceal inflammation. This will be determined via review of pathology reports. *Missed appendicitis* is when a patient presents for the evaluation of abdominal pain, is discharged home, and returns within 1 week with appendicitis. Missed appendicitis will be identified through review of automated EHR data for all patients with appendicitis. As described above, under exclusion criteria, patients who are transferred for definitive care and whose final pathology and surgical reports are not available will not be included in the assessment of safety outcomes.

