**Table 7. Example Enrollment Table**

|                                                      | HP                         |                       | KP                         |                       |
|------------------------------------------------------|----------------------------|-----------------------|----------------------------|-----------------------|
|                                                      | Intervention
2 clusters | Control
2 clusters | Intervention
4 clusters | Control
4 clusters |
| Pre-Intervention period (n)                   | 204                 | 75             | 853                 | 767            |
| Per cluster (n)                               | 102                 | 38             | 213                 | 192            |
| Goal per cluster (n)                                 | 200                        | 200                   | 200                        | 200                   |
| Intervention period (n)                              | 114                        | 88                    | 317                        | 240                   |
| Projected annual                                     | 342                        | 264                   | 1268                       | 960                   |
| Projected over 2-year
intervention period | 684                 | 528            | 2536                | 1920           |
| Projected per cluster (n)                     | 342                 | 264            | 634                 | 480            |
| Goal per cluster                              | 400                 | 400            | 400                 | 400            |

Missed eligibles may occur at several stages. First, the Triage BPA may not fire due to changes in workflow and timing of nurse charting of chief complaint. Second, the Triage BPA may not be completed, thus eligibility cannot be confirmed. Third, patients with final diagnosis unavailable, perhaps due to transfer to an outside facility, cannot be captured.

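### Sections 3a and 7a give opposite instructions on whether outside surgical transfers with unobtainable notes stay in the primary CT and ultrasound analyses

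*Combined protocol and SAP*

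**What the plan says.** All passages are in the combined protocol and SAP.

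- **Section 3a, Exclusion Criteria.** For outside-network surgical transfers with unreviewable notes, "they will be excluded from the safety analyses". For imaging the instruction is the reverse: "These patients will be retained in the primary analyses, evaluating the use of CT or US". Their diagnosis is assigned from what was known when they left the ED.
- **Section 7a, Capturing Transfer Patients (text after Figure 3).** For patients transferred out of either system for surgery with unreviewable notes, "we will exclude them from the primary analyses because we cannot confirm appendicitis based on our definition". Then: "In sensitivity analyses we will explore inclusion of these patients with classification of final diagnosis". No hypothesis is named.
- **Section 6b, paragraph on Hypothesis 1.** "If we are unable to verify final diagnosis, the patient will be excluded from primary analyses", followed by: "These patients may be included sensitivity analyses with the diagnosis of appendicitis or not appendicitis assigned based on provider impression".
- **Section 6b, safety outcomes.** Referring back to the exclusion criteria, patients whose final reports are unavailable "will not be included in the assessment of safety outcomes".
- **Section 9, text after Table 7.** Among the ways in which eligible patients are missed: "patients with final diagnosis unavailable, perhaps due to transfer to an outside facility, cannot be captured".

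Section 6b takes CT and ultrasound use from completed orders at the index ED visit. Section 6a (Hypotheses 2 and 3) states an intent-to-treat approach.

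**The concern.** Sections 3a and 7a describe the same patients, use the same term for the main analyses, and say opposite things. Each could be followed to the letter and produce a different dataset for Hypotheses 2 and 3. The choice would then be open at the time of analysis, when imaging by arm may already be visible.

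The 7a rule would also be the wrong one for imaging. Its reason is that appendicitis cannot be confirmed, but whether a child had a CT at the index ED does not depend on that. In the intervention period, transfer follows randomisation. The decision support gives advice on ultrasound, observation and surgical consultation (Appendices A and B, recommendations by risk group), so it could affect who is transferred. Dropping patients on that event would conflict with the intent-to-treat statement.

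**Working it through.** **1. The rules side by side**

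| Place | CT/ultrasound analyses | Diagnosis-dependent analyses | Diagnosis at transfer used in |
|---|---|---|---|
| 3a | Retained | Excluded from safety | Primary analysis |
| 7a | Excluded, if its wording covers them | Excluded | Sensitivity analysis |
| 6b, Hypothesis 1 | Not clear | Excluded | Sensitivity analysis |
| 6b, safety | Not addressed | Excluded | Not addressed |

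The clear conflict is 3a against 7a. The Hypothesis 1 paragraph is ambiguous: predictive values need a verified diagnosis, so its wording may mean Hypothesis 1 only. It does not say so, and section 6a makes the triage cohort the analytic sample for Hypotheses 2 to 4.

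**2. What exclusion would do to the CT comparison**

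There is no plan figure to reproduce. Let p be the CT rate in all enrolled patients of an arm, t the share who are unverified transfers, and c the CT rate among them. After exclusion the observed rate is (p − t·c)/(1 − t). The plan gives p = 30% at baseline (sample size section). It gives neither t nor c; those below are assumptions. With no true effect, p = 30% in both arms:

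| t control / intervention | c | Control | Intervention | Ratio |
|---|---|---|---|---|
| 5% / 5% | 70% | (0.30 − 0.035)/0.95 = 0.279 | 0.279 | 1.00 |
| 2% / 4% | 70% | (0.30 − 0.014)/0.98 = 0.292 | (0.30 − 0.028)/0.96 = 0.283 | 0.97 |
| 5% / 10% | 70% | 0.279 | (0.30 − 0.07)/0.90 = 0.256 | 0.92 |
| 5% / 10% | 10% | (0.30 − 0.005)/0.95 = 0.311 | (0.30 − 0.01)/0.90 = 0.322 | 1.04 |

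With everyone kept, every row gives 1.00.

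**3. The planned estimator**

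The plan fits a log-linear model with a period-by-arm interaction, so the relevant quantity is the ratio of post/pre ratios. Take c = 70%.

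- Stable difference, 10% in the intervention arm and 5% in control in both periods: (0.256/0.256)/(0.279/0.279) = 1.00. It cancels.
- Share of 5% everywhere before go-live, rising to 10% in the intervention arm only: (0.256/0.279)/(0.279/0.279) = 0.92. It does not cancel.

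So a spurious effect needs a change with go-live in the share or in the CT rate of these patients. Separately, with a true reduction, exclusion changes the population described. With t = 5% and c = 70% in both arms and overall rates of 30% and 22.5%, the ratio among those kept is [(0.225 − 0.035)/0.95]/0.279 = 0.200/0.279 = 0.72, against 0.75 in all enrolled.

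**4. How large the group could be**

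Of about 12,600 anticipated enrolled patients (Protection of Human Subjects), 2%, 5% and 10% are 252, 630 and 1,260. Table 7, an example table, projects 684 HealthPartners and 2,536 Kaiser intervention patients (3,220), and 528 and 1,920 controls (2,448). If unverified transfers arose only at HealthPartners:

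- 10% of 3,220 is 322, or 47% of the 684; 5% of 2,448 is 122, or 23% of the 528.
- 4% of 3,220 is 129, or 19% of the 684; 2% of 2,448 is 49, or 9% of the 528.

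The 5% / 10% rows are therefore best read as an outer case.

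**The case against.** The strongest reply is that the plan already shows which rule governs imaging. Section 3a is the only passage that names the outcome, the safety paragraph in 6b points back to it, and the imaging paragraphs in 6b contain no such exclusion. Section 7a exists to establish final diagnoses, and its stated reason concerns diagnosis. Read by purpose, 7a lacks a qualifier and does not set up a rival imaging analysis. That is probably what was intended, but the unqualified opposite instruction is still there. The draft CONSORT diagram and Figure 3, which might settle it, are not visible in the text reviewed.

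Three stronger readings are tempting and are not supported:

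- **That two sections plainly contradict 3a.** Section 6b's wording sits under the Hypothesis 1 heading and is only ambiguous. The missed-eligible text in section 9 concerns enrolment reporting; it sits badly with 3a but sets no analysis rule.
- **That the loss is large.** Section 7a does say that many children at the prime site are transferred, but that describes all transfers. Most are expected to go to Children's, where a monthly linkage seeks the diagnosis; Kaiser has four paediatric surgical hubs among its 11 sites. The exclusion applies to the remainder.
- **That the CT result would be biased in a known direction.** No document figure shows that the intervention changes these transfers. Stable differences between sites cancel in the planned model, and transfers in the pre-intervention period precede go-live.

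**Conclusion.** The point holds as a contradiction about the analysis population for Hypotheses 2 and 3, and the plan is wrong as written. Applied to those hypotheses, 7a would remove patients with known imaging outcomes, against the intent-to-treat statement.

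Bias is a possibility, not a finding. A spurious effect requires the decision support to change the share of unverified transfers or their CT rate. In the scenarios shown, the null CT rate ratio ranges from 0.92 to 1.04, all on assumed shares and scan rates, with 1.00 when these match across arms. The size of the affected group and the direction of any bias cannot be determined from the documents.

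**What to change.** 1. State once that every enrolled patient stays in Hypotheses 2 and 3, including transfers with an unverified diagnosis, as 3a already says.
2. In 7a and in the Hypothesis 1 paragraph of 6b, restrict the exclusion to analyses that need a verified diagnosis: Hypothesis 1 predictive values, perforation, negative appendectomy and missed appendicitis.
3. For those analyses, report the number excluded by arm and by period (pre-intervention and intervention), alongside the sensitivity analysis that uses the diagnosis at transfer.
4. In section 9, reword the third missed-eligible reason so that these patients are not counted as missed for Hypotheses 2 and 3.

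The cost is wording in 7a, 6b and section 9, plus one table of counts. No new data are needed, because index-visit imaging is already extracted. The change should be made before imaging by arm is examined.

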## b) Ongoing reporting

Study enrollment and use of the CDS will be monitored and reported on a weekly and/or monthly basis using automated data. Use reports will be shared with ED leaders and staff to encourage ongoing use of the tool. This approach has proved successful in previous projects.

Internal reporting, to promote continued CDS use, will vary by site. At HealthPartners, we will report responses to the Triage BPA for the 6 participating sites and risk score calculation for the intervention sites, on a monthly basis, with additional weekly reporting as needed.

### Examples of Use Reports:

[figure not shown]

### Enrollment reporting, by Cluster and health system

\*Column A: Starting with cc of abdominal pain and excluding; left prior to being seen, had prior ED visit, trauma, pregnant, chronic condition/medication, or prior appendectomy, and for HP only BPA did not fire

\*\*Column B: Screening questions not completed includes 1) nurse not completing BPA questions at HP, provider not completing questions via BPA or CDS at HP, provider not accessing RISTRA at KP.

\*\*\*Column C: Screening questions; is abdominal pain diffuse, is there right sided abdominal pain, pain for 5 days or less

|                            |         | Column A*                       | Column B**                              | Column C***                                 | Column D       | Column E                                               |
|----------------------------|---------|---------------------------------|-----------------------------------------|---------------------------------------------|----------------|--------------------------------------------------------|
| Label                      | Site(s) | Potential eligible patients (n) | Screening questions not completed n (%) | Excluded based on screening questions n (%) | ENROLLED n (%) | # months in study (starting with intervention go live) |
| HP Cluster 1 intervention  |         |                                 |                                         |                                             |                |                                                        |
| HP Cluster 1, control      |         |                                 |                                         |                                             |                |                                                        |
| HP Cluster 2, intervention |         |                                 |                                         |                                             |                |                                                        |
| HP Cluster 2, control      |         |                                 |                                         |                                             |                |                                                        |
| KP Cluster 1, intervention |         |                                 |                                         |                                             |                |                                                        |
| KP Cluster 1, control      |         |                                 |                                         |                                             |                |                                                        |
| KP Cluster 2, intervention |         |                                 |                                         |                                             |                |                                                        |
| KP Cluster 2, control      |         |                                 |                                         |                                             |                |                                                        |
| Etc..                      |         |                                 |                                         |                                             |                |                                                        |

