### 3) Study Sites and Population

We will conduct a prospective cluster-randomized clinical trial at 17 general EDs in two large care systems to evaluate the impact of Appy-CDS on CT and ultrasound use, health care outcomes, and direct medical expenditures. We will first measure ultrasound and CT use for 6 months pre-intervention in children identified at triage as at risk for appendicitis presenting for care in a participating ED. We will then group some sites with significant provider cross-coverage and pair within clusters by pediatric volume. We will then randomize half of the clusters to receive the full Appy-CDS. CT and ultrasound utilization in intervention and control sites will be measured for 24 months after the full Appy-CDS “go-live” date. Rates of perforation, negative appendectomies, and missed appendicitis will be monitored as safety outcomes. We will compare resource use and re-visit rates between intervention and control EDs within 7 days of the index ED visit. Figure 2 is an overview of the study design.

This study includes 17 general EDs operated by two health systems: HPMG (Regions, Hudson, Lakeview, Methodist, Westfield and Amery), in the Upper Midwest and KPNC (Sacramento, Roseville, South San Francisco, San Rafael, Santa Clara, South Sacramento, San Leandro, San Francisco, Fremont, Oakland and Richmond). These 17 EDs provide care to a diverse pediatric patient population (34% Hispanic, 19% African-American, and 11% Asian). None of the participating EDs are university-based; however, 5 EDs have academic affiliations. Most ED clinicians are board-eligible or board-certified emergency medicine physicians. Ultrasound is available at each participating ED, and 5 sites are referral centers for pediatric appendectomies. Each ED currently uses the EpiCare EHR (Verona, WI). Both health systems have agreed to participate and work with the study investigators to create linkages between their EHR and the Appy-CDS tool. Collectively, the 17 participating EDs have more than 650,000 annual ED visits, of which 101,014 are patients aged 5-20 years).

To be included, patients must: a) be 5-20.9 years old on the index date, and b) present to a participating ED with a chief complaint of acute abdominal pain.

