Complete data for the validation of pARC were available for 1426 patients. Across seven clinically actionable risk categories (< 5%, 5-14%, 15-24%, 25-49%, 50-74%, 75-84% and ≥ 85%) the pARC score provided valid risk prediction. The AUC for pARC was 0.85 (95% CI 0.83-0.87).

**Hypothesis 1:** Among pediatric patients with abdominal pain, a triage-based trigger will identify those at risk for appendicitis with a negative predictive value ≥99% and positive predictive value ≥20%.

The purpose of the *Triage CDS* (triage-based trigger) is to reliably identify a study cohort at elevated risk of appendicitis at both the intervention and control EDs. This cohort will comprise the analytic sample used to determine the impact of the Appy-CDS system on our key outcomes of CT and ultrasound use (Hy 2 & 3) and health care costs (Hy 4). In addition, data from *Triage CDS* will be included in the appendicitis risk algorithm (as detailed above). Final content of *Triage CDS* will be based on our previous decision rule, expert opinion, and review of ED workflow; Appendix A demonstrates the questions that are included.

Assessment of the *Triage CDS* will consist of 2 steps. First, the frequency that triage nurses or providers answer questions when prompted in the EHR (pain duration <96 hours, pain on right side, history of emesis, pain with walking) will be identified. Second, among pediatric patients with complete data in the EHR, the negative and positive predictive value of the triage tool will be determined. We hypothesize that among pediatric patients with complete data, the triage tool will yield a positive

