predictive value of at least 20% and a negative predictive value of at least 99%. Due to variation in design, patient load, and number of urgent pediatric presentations, we anticipate considerable differences in data capture across EDs. Identifying these differences will inform optimal site-specific system design and training. If the positive or negative predictive value deviates substantially from our goals, (i.e., a 95% confidence interval for negative predictive value failing to include 99%), before full implementation we will review EHR data for all appendicitis cases and refine our trigger. Following implementation, we will prospectively track the performance of the *Triage CDS* at each site and report performance metrics (sensitivity, specificity, positive predictive value, and negative predictive value). If significant differences are discovered across study sites, we will use site-specific estimates of negative and positive predictive values as covariates in multivariate analysis of our key study outcomes (Hy 2-4).

**Hypotheses 2 and 3:** Appy-CDS implementation will reduce CT and total diagnostic imaging (CT and ultrasound) in patients identified as at risk for appendicitis.

Effectiveness of the full Appy-CDS system will be evaluated using a cluster-randomized trial. We will include data from both the pre and post intervention periods in the analysis to account for site-specific variation and potential imbalances in baseline imaging use. Our analysis will follow an intent-to-treat approach and consider both randomization and the timing of the Appy-CDS implementation at the particular study site. Patient and ED- level confounding will be addressed in three ways. First, our paired randomization scheme will attempt to balance potential confounders across study arms before Appy-CDS implementation. Second, we will use a pre- post intervention design to account for imbalances at baseline in imaging use. Third, before final analysis, we will compare patient characteristics across study arms and randomized pairs. If ED or patient-level characteristics deviate in the control and intervention arms, they will be adjusted for in multivariable models.

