We will compare ED visits for the target age group with abdominal pain as a chief complaint to confirm either cohort entry or intentional exclusion. Those who appear to be eligible but not included in the cohort will be listed as missed eligible. On a quarterly basis we will review missed eligible cases and review for cases of appendicitis in this group.

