## Provider selects or enters reason for not completing triage questions.

Research (1 Advisory)

Based on chief complaint, patient is eligible for the Pediatric Abdominal Pain study. After you examine the patient, click the blue hyperlink below to complete up to 3 questions. If appendicitis is not part of your differential diagnosis, please select an acknowledgment reason.

Acknowledge reason:

Epigastric or left sided pain | Chronic abdominal pain | Previous appendectomy | Other reasons (add comments)

Go to Abdominal Pain Additional Assessment Questions.

Refresh Last refreshed on 9/29/2016 at 12:02 PM Accept

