## Appendix B: Intervention Design and Workflow- KP

### a) Capturing eligibility: RISTRA

The analogous triage alert at KPNC will be implemented using the RISTRA interface existing at KPNC. For patients with a chief complaint of abdominal pain, ED providers will be trained to click on the RISTRA icon embedded within the EHR.

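### For intervention-period visits, entry to the H2/H3 cohort depends on staff completing screening by routes that can differ between arms, and no all-visits analysis checks for selection bias

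*Combined protocol and SAP*

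**What the plan says.** Section 3 puts a pre-intervention measurement period first, and then: "We will then randomize half of the clusters to receive the full Appy-CDS". Section 6, Hypotheses 2 and 3, states: "Our analysis will follow an intent-to-treat approach" and "We will include data from both the pre and post intervention periods in the analysis". The effect is a time-by-treatment interaction.

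The population is narrower than all eligible visits. Section 6, Hypothesis 1, says of the group found by the triage screen: "This cohort will comprise the analytic sample used to determine the impact of the Appy-CDS system". In the enrolment report (section 7b), Column B holds visits whose screening questions were not completed, whether because the nurse did not answer or because of "provider not completing questions via BPA or CDS at HP, provider not accessing RISTRA at KP". Those visits are not enrolled. Section 9, below Table 7, confirms that without a completed triage alert eligibility cannot be established.

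The routes into screening are as follows.

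- **HP, both arms:** an automatic triage alert goes to the nurse. If it is unanswered, an alert goes to the provider, which reads: "If appendicitis is not part of your differential diagnosis, please select an acknowledgment reason".
- **HP, intervention EDs only:** the full CDS asks about pain location and duration again and accepts data typed in directly when none arrive from the EHR (Appendix A c).
- **KP, both arms:** "ED providers will be trained to click on the RISTRA icon embedded within the EHR" (Appendix B a).
- **KP, intervention EDs only:** RISTRA also returns the risk score, and ordering CT or ultrasound triggers a reminder about that score (section 5b).

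On visits that are not captured, section 9 says: "Those who appear to be eligible but not included in the cohort will be listed as missed eligible". They are reviewed quarterly for appendicitis. No imaging analysis of them is described.

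**The concern.** An ED-randomised comparison of CT rates is protected by randomisation only if the visits counted in each arm are chosen in the same way. Here a staff action after go-live decides whether a visit counts, and that action is tied to the intervention more closely at intervention EDs.

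Completion is also plausibly related to the outcome. The HP fallback alert diverts clinicians who are not considering appendicitis, and the same suspicion drives imaging. At intervention EDs an imaging order itself prompts use of the tool.

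If go-live changes which visits are captured in one arm, the measured CT rate moves without any change in practice, or a real change is hidden. The protocol recognises this type of hazard elsewhere: its case for waiving patient consent (section 8b) rests partly on selection effects that consent would introduce.

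**Working it through.** **1. Are unscreened visits left out?** Inputs are the Appendix C example report for HP site 101, November 2016 to April 2017. Column A is chief-complaint visits minus those who left early, had a prior visit, trauma, pregnancy, no alert fired, chronic illness or medication, or prior appendectomy. Enrolled = Column A − not completed − screened out.

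| Month | Visits | Removed before Column A | Column A | Not completed | Screened out | Computed | Stated |
|---|---|---|---|---|---|---|---|
| Nov | 79 | 15 | 64 | 37 | 10 | 17 | 17 |
| Dec | 57 | 14 | 43 | 10 | 14 | 19 | 19 |
| Jan | 68 | 14 | 54 | 15 | 21 | 18 | 18 |
| Feb | 71 | 18 | 53 | 23 | 14 | 16 | 16 |
| Mar | 68 | 23 | 45 | 18 | 12 | 15 | 15 |
| Apr | 74 | 19 | 55 | 27 | 12 | 16 | 16 |
| Total | 417 | 103 | 314 | 130 | 83 | 101 | 101 |

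All six stated counts reproduce, and only when non-completed visits are subtracted. Non-completion is 130/314 = 41% (monthly range 23% to 58%; 93/250 = 37% without November). Completion is 184/314 = 59%. Table 3 still lists a pre-intervention meeting in spring 2017, so these months appear to be baseline. They show how much room there is for capture to change, not a difference between arms.

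**2. How many eligible visits could be lost?** Among screened visits, 101/184 = 54.9% were eligible. If the same held for unscreened visits (assumption), 130 × 0.549 ≈ 71 eligible visits were missed at this site.

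**3. How unequal must completion be to matter?** Let p be the true CT rate, c1 completion for visits with CT, and c0 completion for visits without. Then

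observed rate = p·c1 / (p·c1 + (1 − p)·c0).

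Assumptions: baseline CT 30% (sample size section); overall completion 59%; capture unrelated to CT in the control arm and in the pre-period. Table 1 plans for reductions of 20% (to 24%) and 25% (to 22.5%).

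- No true effect, observed 24%: c0/c1 = (0.76/0.24) × (0.30/0.70) = 1.36, so c1 = 0.586/(0.30 + 0.70 × 1.357) = 47% and c0 = 64%.
- No true effect, observed 22.5%: c0/c1 = (0.775/0.225) × (0.30/0.70) = 1.48, giving c1 = 44% and c0 = 65%.
- True fall to 24%, observed 30%: c1/c0 = 1.36, giving c0 = 0.586/(0.24 × 1.357 + 0.76) = 54% and c1 = 73%.

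The completion rates by CT status are hypothetical; the documents give none.

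**4. Does Table 7 show capture moving by arm?** Ratio of intervention-period to pre-period enrolment, intervention over control:

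- HP: (114/204)/(88/75) = 0.48 (95% CI 0.32 to 0.70)
- KP: (317/853)/(240/767) = 1.19 (95% CI 0.98 to 1.44)

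The intervals are Poisson and ignore clustering. The table is headed as an example and has no denominators, and the two systems move in opposite directions.

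**5. Do the planned safeguards reach this?** Difference-in-differences removes stable differences between EDs in capture, not a shift at go-live in one arm. Covariate adjustment works on visits already in the cohort. Multiple imputation is confined to patients already identified as at risk. Missed-eligible review looks for appendicitis, not imaging.

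**The case against.** The strongest reply is that screening is shared by design. The HP triage alert and provider fallback run at all participating EDs, and RISTRA is the KP screen in both arms. Recruitment incentives and use feedback are planned for all sites (section 3b), and triage responses are reported for all six HP sites (section 7b). Entry through the CDS at HP is explicit only in a report footnote. Section 5a has the triage step identify the group before the CDS acts, Appendix A c) shows the full-CDS alert when triage criteria are met, and the data dictionary derives eligibility from triage variables. Completion is also already watched: Hypothesis 1 measures how often questions are answered, Column B is tabulated by cluster and arm, and eligibility and enrolment go to the IDMC every six months.

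Much of this stands, and it rules out several stronger readings that a reader might draw.

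- **That the whole cohort is selected after randomisation.** Pre-intervention visits are screened before it.
- **That CDS use is an established entry rule in the intervention arm.** The HP passages conflict and must be reconciled. At KP the entry tool is common to both arms; only what it returns differs.
- **That Table 7 demonstrates bias.** It cannot, for the reasons in step 4 of the working.
- **That bias would favour the intervention.** Order-triggered prompts could preferentially add imaged visits and hide a benefit.
- **That the intent-to-treat label is simply false.** Analysis by allocated ED regardless of CDS use is a fair meaning of it.

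What does not stand is that monitoring completion is enough. It may reveal a shift in capture, but no planned H2 or H3 analysis would show whether the CT result survives it.

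**Conclusion.** The point holds as a gap in the analysis plan. Entry of intervention-period visits depends on staff behaviour after randomisation, the route can differ by arm, and no planned analysis is free of that dependence. The resulting bias has unknown direction and size. The scope for it is shown by 41% non-completion at one example HP site, apparently at baseline. If overall completion stays near 59% and baseline CT is 30%, a completion ratio of about 1.36 between visits without and with CT, arising only at intervention EDs after go-live, would equal the smaller planned effect; the same ratio reversed would conceal it. Whether any such imbalance occurs cannot be known from the documents. This is a cheap improvement to the plan, not evidence that the trial's comparison is invalid.

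**What to change.** Pre-specify a supportive (sensitivity) analysis of H2 and H3 with the same model on all visits aged 5-20.9 with a chief complaint of abdominal pain that pass the automated EHR exclusions, regardless of screening or CDS use. This is Column A, with visits where the HP alert did not fire added back (1 + 0 + 1 + 0 + 0 + 3 = 5 at site 101, so 319 visits). Report screening completion by arm and period beside the results. Describe the primary cohort as completed-screening visits analysed by allocated ED. Reconcile section 5a, Appendix A c) and the section 7b footnote on whether answers given in the CDS can confer eligibility. If the two analyses differ, interpret the difference; a rule that they must agree in direction would be arbitrary.

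The cost is one more run of the same model. Imaging comes from completed Epic orders (section 6b), and the Hypothesis 1 data dictionary already lists CT and ultrasound orders, exclusion flags and a code for an alert that did not fire. The downside is dilution. If 54.9% of Column A visits are truly eligible and the rest show no effect (assumptions), a 6-point fall (30% to 24%) becomes 0.549 × 6 = 3.3 points, so this analysis should support the primary one, not replace it.
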